#### Questionnaires

Patients will be sent a questionnaire four weeks after their index consultation. The questionnaire will include questions on satisfaction and health status (as discussed above). The covering letter will contain a section for patients who do not wish to participate or receive any further contact in relation to the study. These patients will be asked to send back a blank questionnaire in a prepaid envelope as an indication that they wish to have no further contact. These patients will not receive any further communication in relation to the study. The questionnaire will contain a section at the end, which will offer the opportunity for patients who are willing to complete a questionnaire, to opt out of having their case notes reviewed (for further details see the section, Informed consent). Those who do not respond will be sent two reminder letters with a second copy of the questionnaire two and four weeks after the first mail-out.

#### Case note review

Research staff will undertake a review of case notes of patients who have consented to have their notes reviewed (see below for further details of procedure for obtaining informed consent). This will take place a minimum of twelve weeks after their initial same day consultation. The case note review will be undertaken in the relevant GP surgery and patients’ notes will not leave the surgery. The purpose of the review will be to record information on the number and type of healthcare contacts including casualty contacts and hospital admissions, and length of consultations where this information is available. Laptops or memory sticks (encrypted as per NHS security requirements) will be used by researchers to record encrypted data in the research database. A standardised process will be adopted when searching notes.

Although it is not possible to blind research staff to the trial arm that a practice has been allocated due to the cluster design, a small validation study will be undertaken to explore the impact of lack of blinding on the outcome assessment process. During the feasibility study, a small sample of notes (30 from one practice) was independently examined by the four trial researchers, and the relevant data extracted. The inter-rater reliability of the data extraction process was assessed, and any divergence between assessors documented and resolved with a view to developing standardised procedures to guide the review process in the main trial.

### Statistical analysis

Analyses will also take into account the additional CONSORT guidelines for cluster-randomised trials and pragmatic trials
[3,4]. The full combined statistics and health economics plan has been reviewed by the Trial Steering Committee and Data Monitoring Committee and is available from the authors. A summary of proposed analyses is provided below.

The primary analysis will be based on an intention-to-treat (ITT) principle, that is, analysis of all trial patients in practices according to random allocation. It is assumed that the vast majority of patients in the two triage arms will receive the triage intervention, with only a few being managed in other ways. For the usual care arm, there is no intervention beyond the management the patient would receive if the trial were not taking place and hence no patients can fail to receive the intervention. The primary analysis will take the form of a random effects regression analysis taking account of the hierarchical nature of the study design (that is, allocation by practice) and to allow for adjustment for practice-level minimisation variables (geographical location, deprivation level and size of practice) and patient-level baseline covariates shown to differ (based on descriptive data) at baseline. There is potential for clustering by clinician with the practices; the magnitude of this effect will be estimated and where necessary incorporated in the data analysis. However, this is a pragmatic trial where the intervention is being delivered at the practice level, rather than at the level of individual clinicians. The same primary analysis models will be fitted for the primary outcome, secondary outcomes and costs. A generalised linear model (GLM) will be fitted with the appropriate choice of family and link function, according to the type of data and its properties. The intracluster correlation coefficient (ICC) will be reported for all primary and secondary outcomes. The individual components of the primary outcome, the patient experience questions, and the five individual questions that comprise the EQ-5D will be reported for each group descriptively. A secondary (per protocol) analysis will be performed (for the primary outcome only) as a secondary analysis if there are sufficient patients (for example, > 1%) in the triage arms who do not receive triage. In such an analysis, these patients would be excluded, such that only patients who receive the triage intervention are included.

The influence of practice-level characteristics (for example, deprivation, location and list size) on the primary outcome will be investigated using interaction terms. Although the power to detect moderate subgroup interactions will be low, we are primarily interested in investigating the possibility of large interactions, which are qualitative (the direction of treatment effects varies between subgroups) rather than quantitative (the magnitude of the treatment effect varies between subgroups, but not the direction). This subgroup analysis will be restricted to the primary outcome.

Sensitivity analyses will be conducted to investigate the potential impact of missing data on the primary outcome only. These will include making different assumptions such as best-case scenarios (for example, assuming a patient who does not consent to a case notes review has zero healthcare contacts in the four-week period following the initial telephone call requesting a same-day appointment), as well as multiple imputation models. Available demographic characteristics (depending on whether questionnaire is completed) of patients who consent to the case notes review will be compared to those who do not.

The primary economic analysis will estimate the mean cost of care across each of the trial arms, to include triage (where used) and the items in the primary outcome. Economic analyses will be based on a micro-level costing estimate for the triage intervention, and the use of published unit cost data for other elements of resource use. Estimates of the cost associated with triage interventions will be based on incremental costs when compared to usual care, with any capital costs and/or training costs depreciated/spread over an appropriate time period in the primary analyses (with other time horizons for these costs explored in sensitivity analyses).

The economic evaluation will present between group comparisons of costs using the regression-based statistical methods described above. Mean participant-level cost estimates for the triage interventions will be presented, with 95% CI. Although cost data often does not follow a normal distribution and parametric tests are therefore not appropriate, if a sample has a large number of observations as in this case (circa 18,000), incorporating central limit theorem implies parametric tests are appropriate and may be used
[9].

Sensitivity analyses will be undertaken to explore the implications of uncertainty in data used, and assumptions made within the analyses. Exploratory analyses will be undertaken to estimate the costs associated with same-day primary care resource use, using trial data from the primary analyses combined with unit cost data, and also using data collected within the trial on a sample of same-day GP and nurse contacts (triage arms and usual care) to inform a more micro-level estimate of time spent in primary care on the same day as the triage index consultation.

Emphasis will be placed on estimation rather than hypothesis testing. Where hypothesis tests are carried out, these will be at the 5% level for primary and secondary outcomes, and the 1% level for interaction terms. While we adjust *P*-value cutoffs for the three-arm nature of this trial (that is, three independent between-group comparisons) we will not adjust for multiplicity of outcomes as such methods are too conservative when outcomes are positively correlated, as they would be in this trial. However, all analyses will be planned a priori and reported in full. All analyses will be conducted using Stata v.11. No interim analyses are planned.

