**Methods/design:**

ESTEEM is a pragmatic, multi-centre cluster randomised clinical trial with patients randomised at practice level to usual care, computer decision-supported nurse triage, or GP-led triage. Following triage of 350–550 patients per practice we anticipate estimating and comparing total primary care workload (volume and time), the economic cost to the NHS, and patient experience of care, safety, and health status in the 4-week period following the index same-day consultation request across the three trial conditions.

We will recruit all patients seeking a non-emergency same-day appointment in primary care. Patients aged 12.0–15.9 years and temporary residents will be excluded from the study.

The primary outcome is the number of healthcare contacts taking place in the 4-week period following (and including) the index same-day consultation request. A range of secondary outcomes will be examined including patient flow, primary care NHS resource use, patients’ experience of care, safety, and health status.

The estimated sample size required is 3,751 patients (11,253 total) in each of the three trial conditions, to detect a mean difference of 0.36 consultations per patient in the four week follow-up period between either intervention group and usual care 90% power, 5% alpha, and an estimated intracluster correlation coefficient ICC of 0.05. The primary analysis will be based on the intention-to-treat principle and take the form of a random effects regression analysis taking account of the hierarchical nature of the study design. Statistical models will allow for adjustment for practice level minimisation variables and patient-level baseline covariates shown to differ at baseline.

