#### Usual care

Practices will be asked to continue with their standard consultation management systems for handling same-day consultation requests. We intend to describe in detail the systems used in usual care practices. All practices will be asked to complete a short questionnaire to collect details on their current staffing arrangements and systems to manage same-day consultation requests, including the extent to which they use triage of any sort, and their current appointment system arrangements.

Following training for intervention practices, practice systems will be allowed to stabilise to the allocated condition during a four-week run-in period prior to a five-week intervention and patient recruitment period.

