We will survey patients who have requested same-day consultations in each of the three trial conditions using a modified version of the national survey instrument. Whilst the national survey explores patients’ experiences of care in the past 6 months, we will modify relevant questions to focus on the participants’ recent experiences of care following their same-day consultation request.

The responsiveness of the consultation management system will be assessed using patient reports of care received (for example, how quickly care was provided and overall satisfaction) and their evaluations (using a 5-point Likert scale)
[41,42] of the timeliness and convenience of the response
[43] to the original same-day consultation request incorporated into the follow-up questionnaire.

For patient safety, deaths within 7 days of the same-day consultation request (from practice records), and attendance at A&E within four weeks and number and length of stay of emergency (unplanned, that is, admission with no evidence of prior planning of that admission within a one-day period at notes review) hospital admissions within 7 days of the index consultation (from primary care records examined twelve weeks after the same-day consultation request).

Patient health status will be assessed by the widely used EuroQol Group 5-Dimension Self-Report Questionnaire (EQ-5D) measure
[44] incorporated into the follow-up questionnaire, along with a question on problem resolution
[27,28] (5-point Likert scale).

For descriptive data, we will collect patient-level (for example, on age and gender) and practice-level (for example, on practice size, staffing and deprivation index) data. Two approaches to defining patient casemix will be adopted: (i) we will record morbidity on the basis of the principal systems involved (after
[28,29]), allowing for clinicians to record up to three systems in respect of each consultation; (ii) an 8-point score will be used to define the complexity of the case (after Howie
[45]) with each consultation being defined as having substantial (2 points), attributable (1 point) or no content (0 points) in respect of each of four domains, namely, physical, social, psychological or other (for example, administrative) components to the consultation.

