### Data collection

#### Clinician data collection forms

Clinicians will complete a short data collection form (clinician form) at the time of the initial consultation following a patient’s same-day request (triage or usual care contact). This form captures details of the consultation including which health professional undertook the consultation, whether the patient did not attend, case-mix (see Secondary outcomes, Descriptive data), treatment and management options chosen (for example, ordering of tests, recommending subsequent appointment or referral), start and end time of the consultation and the patient’s response to the initial verbal consent to note review, which the clinician asks for at the end of the consultation.

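### Patient-level covariates enter the primary model only if they look imbalanced, and the wording does not keep out case-mix that unblinded clinicians record after allocation

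*Protocol article*

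**What the plan says.** The Statistical analysis section describes a random effects regression with two groups of adjustment variables. The practice-level group is named: location, deprivation and practice size. The patient-level group is defined only by a rule: "patient-level baseline covariates shown to differ (based on descriptive data) at baseline". The abstract repeats it: "Statistical models will allow for adjustment for practice level minimisation variables and patient-level baseline covariates shown to differ at baseline". No covariate, threshold or test is attached to the rule, and its reach is wide: "The same primary analysis models will be fitted for the primary outcome, secondary outcomes and costs". The same section undertakes that all analyses will be set beforehand and fully reported.

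Under Secondary outcomes, one paragraph describes the descriptive data. It opens "For descriptive data, we will collect patient-level (for example, on age and gender) and practice-level" and goes on to two case-mix measures: body systems recorded by the clinician, and "an 8-point score will be used to define the complexity of the case". Clinician data collection forms says where these come from. The form is completed at the first contact after the request, whether triage or usual care: "This form captures details of the consultation including which health professional undertook the consultation". Case-mix is listed among its items, with a pointer back to the descriptive data paragraph. The Blinding section states that practitioners cannot be blinded. According to Usual care, training and a four-week run-in come before patient recruitment.

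**The concern.** There are two linked problems.

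First, observed imbalance is the wrong criterion for entry. A strongly prognostic covariate that happens to balance is left out, and a weak one that happens to differ goes in. The rule is written down beforehand, but the model it produces is not known until the data are seen. With whole practices randomised, patient characteristics that cluster by practice can differ between arms by chance more often than under individual randomisation.

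Second, the rule relies on descriptive data, and the article uses that phrase as the label for a set that includes clinician-scored case-mix. That score is not a baseline measurement. It is made after allocation, by staff who know the allocation, and in the triage arms by the person delivering the intervention by telephone. In usual care the contact may be face to face. The score could therefore differ between arms because of mode and assessor alone. Read literally, the rule could treat that difference as baseline imbalance and adjust for it. Adjusting for a variable that allocation affects can bias the treatment effect.

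**Working it through.** **Plan's own figures.** From Sample size: difference 0.36, SDs 0.78 and 1.79, 5% alpha (taken as two-sided), 90% power.

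- Pooled variance: (0.78² + 1.79²)/2 = 1.906.
- n = 2 × 1.906 × (1.960 + 1.282)²/0.36² ≈ 309.1, rounded up to 310. The article gives 305, within 2%.
- 305 × 12.3 = 3,751.5. The article gives 3,751.

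The figures reproduce, and none of them depends on the covariate rule. They matter here only because they supply the 0.36 yardstick and the cluster structure.

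**Is case-mix inside the rule?** Setting the sections side by side:

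| Question | Source | Answer |
|---|---|---|
| What triggers entry? | Statistical analysis | Differing at baseline, based on descriptive data |
| What are descriptive data? | Secondary outcomes | Age, gender, practice characteristics, body systems, complexity score |
| When is case-mix recorded? | Clinician data collection forms | At the first contact, which is the triage call in two arms |
| Is the scorer blinded? | Blinding | No |
| Is allocation already in force? | Usual care | Yes, after training and run-in |
| Is case-mix called a baseline covariate? | Whole article | No |

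The wording permits case-mix to enter but does not state that it will.

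**How often might a covariate appear to differ by chance?** This is an illustration. The article gives no covariate ICCs and no screening test, so both are assumed. Inputs are k = 14 practices per arm, m = 3,751/14 ≈ 268 patients per practice, and no systematic difference between two arms.

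- Design effect: DE = 1 + (m − 1) × ICC.
- Patient-level screen at p < 0.05 that ignores clustering: P = 2[1 − Φ(1.96/√DE)].
- At least one of five independent covariates flagged: 1 − (1 − P)⁵.
- Alternative screen, a standardised difference above 0.1: its SE is √(2·DE/(k·m)), with k·m = 3,752.

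| Covariate ICC | DE | One flagged, p < 0.05 | Any of five, p < 0.05 | SE of standardised difference | One flagged, difference > 0.1 SD |
|---|---|---|---|---|---|
| 0 | 1.00 | 5% | 23% | 0.023 | below 0.1% |
| 0.01 | 3.67 | 31% | 84% | 0.044 | 2% |
| 0.05 | 14.35 | 60% | 99% | 0.087 | 25% |

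The result depends heavily on how differing is judged, and the article does not say how.

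**What if case-mix were adjusted for?** Suppose allocation shifts the recorded score by s SD, and contacts rise by b per SD of score. Adjustment then moves the estimated arm difference by s × b. Both inputs are assumed; the article gives neither.

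- Low: 0.1 × 0.1 = 0.01 contacts; 0.01/0.36 = 3%.
- Middle: 0.2 × 0.3 = 0.06 contacts; 0.06/0.36 = 17%.
- High: 0.3 × 0.5 = 0.15 contacts; 0.15/0.36 = 42%.

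The direction is not known, because the article does not indicate which arm would score higher.

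**The case against.** The strongest reply is that the parenthesis about descriptive data may mean only that imbalance will be judged descriptively, without significance tests. On that reading it names a method of comparison and not a data set. The rule is also limited to baseline covariates, the patient-level examples are age and gender, and the clinician form sits with details of the consultation. This reply largely stands. A reader might infer that the plan intends to adjust for case-mix, but no sentence says so. What survives is that the article uses the same label for the data set holding case-mix and does not exclude it.

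The section also calls itself a summary of a fuller plan that the oversight committees have reviewed. A list of candidate covariates is ordinary content for that plan, so its absence here is no fault. The criticism is of the published rule, which a fuller plan following it would inherit.

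The analyst is blind to allocation. That limits deliberate selection, but it does not stop the model depending on the data or turn a post-allocation score into a baseline one.

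Patients are identified by receptionists after practices are allocated, so imbalance may be systematic and attention to it has a rationale. That argues for always adjusting for characteristics allocation cannot change, and not for an open-ended rule.

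A reader might also infer that the model should include each practice's existing use of triage, since every practice is asked about its systems, "including the extent to which they use triage of any sort, and their current appointment system arrangements". The documents do not support making that part of this point. Omitting the variable does not bias a randomised comparison. How much triage usual care contains is a feature of the pragmatic comparator, which adjustment would not remove. Nor does the article show that the share of requests triaged is recorded before randomisation.

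**Conclusion.** The point holds as a defect in a stated rule. The article selects patient covariates for the primary, secondary and cost models on observed imbalance, which leaves the model open until the data are seen and is hard to square with planning every analysis in advance. This part rests on the text alone.

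The case-mix part holds only as a risk that the wording allows. If it materialised, the illustrative shift is 0.01 to 0.15 contacts, or 3% to 42% of the 0.36 target. That runs from trivial to material for a workload conclusion, and it depends wholly on the assumed shift and slope. The flagging probabilities likewise depend on assumed ICCs and screens. No effect on the type I error rate has been shown, and none is claimed. The sample size stands.

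**What to change.** In Statistical analysis and in the abstract, replace the imbalance rule with a fixed list used whatever the observed balance: the minimisation variables plus patient age and gender. State that body systems and the complexity score from the clinician form are descriptive, or for a labelled sensitivity analysis only, and do not enter the primary model. Because the same models are used throughout, apply this to the secondary outcomes and costs as well.

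The cost is a few sentences. Age and gender are already to be collected, no new data are needed, and 3,751 per group is unchanged. One practical check remains: the missing-data paragraph suggests that some demographic items depend on questionnaire return. The wording should therefore say that age and gender come from a source available for every analysed patient, such as the practice record used for the notes review.

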### Aims

The overarching aim of this trial is to assess the clinical- and cost-effectiveness of nurse-led, computer-supported telephone triage and GP-led telephone triage, compared to usual care for patients requesting same-day consultations in general practice. Specific objectives of this trial are to compare the effects on primary care workload and cost, and patient experience of care, patient safety and health status, of: (1) nurse-led, computer-supported telephone triage versus usual care for patients requesting same-day consultations in general practice; (2) GP-led telephone triage versus usual care for patients requesting same-day consultations in general practice, and (3) nurse-led computer-supported telephone triage versus GP-led telephone triage.

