### Sample size

Our estimation of sample size is based on the primary outcome of the number of healthcare contacts taking place in the four-week period following the index same-day consultation request. The estimation draws on a previous UK study comparing nurse-led telephone triage to standard practice for handling same-day consultation requests
[3]. That trial reported the number of NHS consultations based on general practice (GP and nurse), A&E and out-of-hours contacts. We believe this to be a good proxy for our primary outcome. Over the four-week follow-up of the trial the authors reported a mean number of NHS consultations of 1.02 (pooled SD 0.78) (Table four in
[3]) in usual care compared to a mean of 1.38 (pooled SD 1.79) in the nurse telephone-triage arm. Estimated trial sample size requirements for this trial are summarised in the table below. Four sample size scenarios are shown based on 80% or 90% statistical power and a intracluster correlation coefficient (ICC) of 0.01 or 0.05 (chosen as they represent the upper end of the average ICC reported from a survey across a range of outcome measures collected in trials from primary care settings
[46]) (see Table
1).

**Table 1 T1:** Sample size calculation

**Number per group***	**ICC**	**Design factor**	**Number of patients per group**	**Final number of patients per group+**	**Number of practices per group**
305*	0.01	3.26	994	1,867	4
305*	0.05	12.3	3,751	7,046	14
228^	0.01	3.26	743	1,396	3
228^	0.05	12.3	2,804	5,267	10

*At 90% power and 5% alpha; ^80% power and 5% alpha (both using the above means and SDs as per text); +after 6%
[3,27,28] of patients being excluded, 10%
[14,28,29] initially declining participation, 30%
[27-29] non-response to the request to return written consent to note review; of responders, 10% decline note review.

Selecting the most conservative sample size scenario (that is, 90% power, ICC 0.05) we estimate we require 3,751 patients per group to detect a difference of the magnitude reflected above (1.02 (0.78) versus 1.38 (1.79) primary care contacts in the follow-up period) in the primary outcome between the nurse-led triage and usual care arms. In order to inform the power study, and prior to undertaking the one-year pilot study (including the requirement for patient-written, rather than verbal consent), which would yield supporting data, we estimated that of all patients requesting a same-day consultation, 6%
[3,27,28] will be deemed ineligible, 10%

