[14,28,29] will initially decline participation in the trial and/or follow-up of their notes, and 30%
[27-29] will not respond to the request to return written consent to note review. Of those who do respond in the questionnaire survey, we estimate 10% (conservative) will decline note review. Thus a total of 7,046 patients seeking same-ay consultations across 14 practices over a five-week period will be required in each of the three trial arms (see Figure
1). In the absence of a published effect size for the primary outcome for the GP-led triage arm, we estimated the sample size requirement on the claimed impact of a 30% reduction in GP workload with the Stour Triage system, and assumed a reduction of 30% in the primary outcome. At 90% power and an ICC of 0.05, a total of 1,983 patients in the GP-triage and usual management arms would be required. However, given the uncertainty of the estimate of a 30% reduction, we propose to recruit the same number of patients requesting same-day consultations as estimated for the nurse-triage arm, that is, 7,046 patients (and 42 practices).

The pilot study provided confirmation of our assumed ICC of 0.05 (that is, 0.03, 95% CI {AU query: CI ok as added?}0.00 to 0.08). Furthermore, the pilot study, led to a change in the method of patient consent to note review from written consent (obtained from completed patient questionnaires) to include verbal consent obtained from the treating clinician. The proportion of patients agreeing to case note review is anticipated to increase from an estimated 63% (original power study) to an estimated 78% under revised, and ethically approved consenting arrangements.

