### Feasibility

An average practice (7,000 patients) accommodates around 714 consultations per week
[10] - approximately 142 consultations per day. Some
[4] have estimated that up to one-third of these are patients seeking same-day consultations; however, case definition is of importance, and we believe that an estimate of around 20 patients per day, 100 per week (14% of workload) clearly seeking same-day consultations is conservative, and reasonable; this was confirmed as realistic following our pilot and feasibility study. To achieve our sample size, we will need to recruit patients in 42 practices, each for a five-week period of patient recruitment. It is acknowledged, however, that practices vary in terms of the number of same-day consultation requests they receive (for instance due to practice size, nature of local population et cetera). To reduce the likelihood of this leading to significantly uneven patient recruitment across the different practices, in practices where the number of same-day consultation requests is significantly above the average, we will randomly sample sufficient numbers of patients from each practice to ensure proportionality across the practices.

For the patient-related outcomes, self-reported health status and perception of access to care will be collected by postal survey distributed from the patient’s registered GP using practice-headed notepaper, and with an estimated response rate after two reminders of 70%
[47-50]. The survey will be distributed four weeks following the index episode of care, to patients who have been identified for the trial. The survey response pack will incorporate written consent to review of the patient’s medical record with a view to capturing primary outcome measure data twelve weeks after the index episode of care. At 80% power and 5% alpha, our sample size of 7,046 per group will allow us to detect an effect size of 0.18 of a standard deviation at an ICC of 0.01 and an effect size of 0.34 of a standard deviation at an ICC of 0.05. Thus, we believe that the proposed sample size will allow us to be able to detect a small to moderate effect size in our patient-reported secondary outcomes.

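### Missing-data sensitivity analyses are confined to the primary outcome, so the patient-reported comparisons rest on questionnaire responders with no planned check for selective reply

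*Protocol article*

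**What the plan says.** The Aims section sets out to "compare the effects on primary care workload and cost, and patient experience of care, patient safety and health status". Under Secondary outcomes, experience, EQ-5D and problem resolution are collected by a single postal questionnaire four weeks after the request. The Feasibility section under Methods/design describes this survey "with an estimated response rate after two reminders of 70" per cent. The Blinding section says that patients and practitioners cannot be blinded.

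The Statistical analysis section fits the same random effects models to primary outcome, secondary outcomes and costs. On missing data it states: "Sensitivity analyses will be conducted to investigate the potential impact of missing data on the primary outcome only". The methods named are best-case scenarios "as well as multiple imputation models", both within that scope. The only comparison planned there between patients with and without data sets those who consent to note review against those who do not.

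On note review, the Sample size section says that consent now includes verbal consent given to the clinician, and that the share agreeing is "anticipated to increase from an estimated 63% (original power study) to an estimated 78% under revised, and ethically approved consenting arrangements". Informed consent describes the same arrangement, with an opt-out on the questionnaire. Feasibility still places written consent to note review in the survey pack.

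**The concern.** Each patient-reported outcome is measured once, and the Economic evaluation section notes that there is no baseline quality-of-life measure. A regression on a single follow-up value takes no outcome information from a patient who did not return the form, so the modelled comparison is one among responders.

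Reply may depend on satisfaction, on whether the problem resolved, or on health. Patients know which system handled their call, so that dependence may differ by arm. An observed difference, or the lack of one, could then partly reflect who replied.

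The planned missing-data work does not reach these outcomes, although the trial collects relevant information outside the questionnaire. The clinician form records case-mix and management at the initial consultation. Note review records contacts, A&E attendance and admissions.

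**Working it through.** **Inputs.** From Table 1 and the Sample size text: 7,046 patients per arm, 6% ineligible, 10% initially declining, 30% not responding, and "of responders, 10% decline note review". From Sample size: 63% rising to 78% for note review. From Feasibility: stated detectable effects of 0.18 SD (ICC 0.01) and 0.34 SD (ICC 0.05) at 80% power. The responder/non-responder gap is in neither place and is assumed below.

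**Reproducing the plan's figures.** Retention is 0.94 × 0.90 × 0.70 × 0.90 = 0.533, and 3,751 / 0.533 = 7,038, against 7,046 stated. Also 0.70 × 0.90 = 63%, as stated. The 30% non-response is therefore the plan's own working assumption.

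**Scale per arm.**
- Surveyed: 7,046 × 0.94 × 0.90 = 5,961.
- Responders: 5,961 × 0.70 = 4,173.
- Non-responders: 5,961 × 0.30 = 1,788.

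**Non-responders with note data**, under the verbal-consent arrangement and assuming that 78% and 70% share a denominator:
- If no responder opts out: (78 − 70) / 30 = 27%, about 480 patients.
- If 10% of responders opt out: (78 − 63) / 30 = 50%, about 890 patients.

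**Bias of the responder-only comparison.** In an arm with response rate r, and gap g (responder mean minus non-responder mean, in SD), the responder mean exceeds the mean of all surveyed by (1 − r)g. The bias in the arm difference is (1 − r₁)g₁ − (1 − r₀)g₀. With 70% response in both arms this becomes 0.30 × (g₁ − g₀):

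| Assumed g₁ − g₀ | Bias | Share of 0.18 SD | Share of 0.34 SD |
|---|---|---|---|
| 0 | 0 | 0% | 0% |
| 0.05 SD | 0.015 SD | 8% | 4% |
| 0.1 SD | 0.03 SD | 17% | 9% |
| 0.2 SD | 0.06 SD | 33% | 18% |

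Unequal response also matters when the gaps are equal. At 60% against 70% response, with a gap of 0.2 SD in both arms, the bias is 0.40 × 0.2 − 0.30 × 0.2 = 0.02 SD.

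**The yardstick.** The stated 0.18 and 0.34 SD did not reproduce. The formula is (1.96 + 0.84) × √(2 × DE / 4,173), with DE = 1 + (m − 1) × ICC. Here m is 227 (implied by the design factor of 12.3) or 298 (4,173 / 14). This gives 0.11 to 0.12 SD at ICC 0.01 and 0.22 to 0.24 SD at ICC 0.05. Against these, a bias of 0.06 SD is about a half and about a quarter. It is a larger fraction, but still a fraction.

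**The case against.** The article calls its analysis section a summary and refers to a full plan that is not shown. Subgroup and per-protocol analyses are also confined to the primary outcome, so the restriction looks deliberate and consistent. These outcomes are secondary. The patient experience questions and the five EQ-5D items are to be reported descriptively, the Economic evaluation section calls its quality-of-life analysis exploratory, and emphasis is placed on estimation. Imputation under missing at random does not correct reply that depends on the outcome itself.

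Much of this stands and limits the point. It does not remove it, because the article does not leave the scope open: it fixes it. The last objection is a reason to add a shifted analysis.

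Four stronger readings are tempting and are not supported:
- That selective reply could by itself create or hide an effect of the stated detectable size. With 30% missing in each arm, that needs a between-arm gap difference of 0.18 / 0.30 = 0.6 SD, or 0.34 / 0.30 = 1.13 SD. Nothing in the documents suggests gaps of that order.
- That the plan forbids any check. It limits the planned sensitivity analyses, does not bar reporting response by arm, and commits to the CONSORT guidance for cluster and pragmatic trials.
- That costs are equally unprotected. Economic evaluation and Statistical analysis promise separate, extensive sensitivity analyses for the economic data. They do not name missing data, but a gap is not established.
- That record data certainly exist for many non-responders. Under the written-consent wording in Feasibility they would exist only for responders.

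**Conclusion.** The point holds for the patient-reported secondary outcomes that are compared between arms: EQ-5D, problem resolution and any experience rating that is modelled. With 30% expected non-response, these comparisons use responders, and the stated plan includes no check for selective reply. That they use responders is inferred from the single measurement and the stated restriction, since the article does not itself describe a complete-case analysis.

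On assumed between-arm gap differences of 0.05 to 0.2 SD, the bias is 0.015 to 0.06 SD, or 4% to 33% of the stated detectable effects. Differential non-response is plausible in an unblinded trial but is not shown. The primary conclusion is unaffected. The change is worth making before analysis because the method is already planned and much of the auxiliary information is already being collected. The 27% to 50% of non-responders with note data depends on the verbal-consent arrangement and on a common denominator.

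**What to change.** In Statistical analysis, remove the restriction to the primary outcome and specify, as sensitivity analyses:

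1. Multiple imputation that respects practice clustering, for EQ-5D, problem resolution and any experience rating compared between arms. Auxiliary variables: arm, the minimisation variables, age and sex where available, clinician-form case-mix and management, and contacts, A&E attendance and admissions from note review.
2. One version with the imputed values shifted by an arm-specific delta, to address reply that depends on the outcome.
3. Response by arm, and a comparison of responders with non-responders on the data held for both.
4. Results shown beside the responder-only analysis.

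Items planned as descriptive need no imputation. Deaths before the questionnaire should be reported separately and not imputed. Separately, reconcile the written-consent statement in Feasibility with the verbal-consent and opt-out statements in Sample size and Informed consent.

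The cost is revised wording and some extra analysis, with no new patients or data. The imputed results rest on a missing-at-random assumption, which is why they accompany the planned analysis and do not replace it.
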